### Assessment

Prospective participants will first contact the investigators by telephone for initial screening and if likely to be suitable they will be asked to complete questionnaires online via the Survey Monkey website and attend for an initial clinical assessment at either the Emotional Health Clinic at Macquarie University ([name], LS, RR) or Drug Health Services at Royal Prince Alfred Hospital (CS, PH). Participants who meet inclusion criteria will be asked to reduce their drinking to “low risk” levels as recommended by NHMRC [66] (males up to 4 standard drinks per day and women up to 2 standard drinks per day) for three days to minimise the transient effects of alcohol use on functioning (e.g., intoxication, anxiety, irritability, sadness and depressed mood) [23,71].

Participants who are likely to require withdrawal management (severe alcohol dependence, previous withdrawal, current score ≥ 20 on CIWA-AR indicating established withdrawal) [70] will be referred to local specialist drug and alcohol clinics or participating general medical practitioners (selected GPs who have been made aware of this study and are willing to provide treatment for study participants). Once withdrawal is completed and the prospective participant has achieved 3 days of no more than low risk drinking, they are invited for the initial clinical interview.

The initial clinical assessment will include the Anxiety Disorders Interview Schedule for DSM-IV (ADIS-IV) [68] and be conducted by a Masters or PhD level Clinical Psychologist. In previous research [51] we have demonstrated high inter-rater reliability for social anxiety disorder (kappa = 0.87) and anxiety disorders in general (kappa = 0.80) using this interview. Participants will also be assessed using questions based on the Avoidant Personality Disorder section of the International Personality Disorder Examination (IPDE) [72].

All interviews will be audio-taped and a random sample of 25% will be rated by a PhD level Clinical Psychologist with relevant diagnostic experience, to determine diagnostic reliability. Measures used in the study are shown in Table 1 and include: the Anxiety Sensitivity Index [73]; Kushner’s Alcohol Outcome Expectancies Questionnaire [74]; the Timeline Follow-Back (TLFB) method for quantifying alcohol consumption over the previous 28 days [75,76]; the Opiate Treatment Index (OTI) to assess drug (and medication) quantity and frequency during the previous 28 days [69]; the Penn Craving Scale [77]; Self efficacy for abstinence [78]; the University of Rhode Island Change Assessment [79], used to assess motivation; Health Service Utilisation questions [80], used to asses other treatment received in study period.

**Table 1 T1:** Schedule of assessments

**Assessment**	**Telephone contact**	**Pre treatment**	**Post washout**	**Post treatment**	**3 month follow-up**	**6 month follow-up**
*Eligibility*						
Alcohol Use Disorders Identification Test (AUDIT) [64]	+	-	-	-	-	-
Mini Social Phobia Inventory (Mini-SPIN) [65]	+	-	-	-	-	-
Clinical Institute Withdrawal Assessment for Alcohol Revised (CIWA-AR) [70]	+	-	-	-	-	-
Suicide Behaviours Questionnaire-Revised (SBQ-R) [81]	+	-	-	-	-	-
Psychosis Screening Questionnaire [67]	+	-	-	-	-	-
Anxiety Disorders Interview Schedule for DSM-IV (ADIS-IV) [82] incorporating International Personality Disorders Examination Avoidant Personality Disorder questions (IPDE) [72]	-	+	-	-	+	-
*Primary outcome measures*						
Social Phobia Scale and Social Interaction Anxiety Scale (SPS/SIAS) [83]	-	+	+	+	+	+
Time Line Follow Back (TLFB) [76]	-	+	+	+	+	+
Severity of Alcohol Dependence Questionnaire (SADQc) [84]	-	+	+	+	+	+
General Health functioning SF12 [85].	-	+	-	+	+	+
Blood for LFTs, FBC, CDT, Electrolytes	-	+	-	-	+(1)	-
*Secondary outcome measures*						
Sheehan Disability Scale(SDS) [86]	-	+	-	+	+	+
Depression, Anxiety and Stress Scale (DASS-21) [87]	-	+	+	+	+	+
Days out of role from the Brief Disability Questionnaire [88]	-	+	-	+	+	+
Drinker Inventory of Consequences (DRINC) [89]	-	+	-	+	+	+
*Static and varying covariates*						
Family Tree Questionnaire (FTQ)		+				
Anxiety Reduction Subscale of the Alcohol Expectancies Questionnaire [90]	-	+	-	+	+	+
Kushner’s Alcohol Outcome Expectancies Questionnaire [74]	-	+	-	+	+	+
Penn Alcohol Craving Scale(PACS) [77]	-	+	-	+	+	+
Alcohol Abstinence Self Efficacy Scale (AASES) [78]	-	+	-	+	+	+
Alcohol Expectancies for Social Evaluative Situations scale (AESES) [91]	-	+	-	+	+	+
Anxiety Sensitivity Index (ASI) [73]	-	+	-	+	+	+
University of Rhode Island Change Assessment (URICA) [79]	-	+	-	+	+	+
*Potential confounds*						
Health Service Utilisation questions [80]	-	+	-	+	+	+
The Opiate Treatment Index (OTI) [69,92]	-	+	-	+	+	+

Notes (1) Blood tests were used to verify abstinence only if baseline tests were elevated when drinking was reported.

Blood will be taken for full blood count (FBC), liver function tests (LFTs) and carbohydrate-deficient transferrin (CDT; a biological marker of recent alcohol consumption), calcium and electrolytes at baseline. If abnormal test results are obtained at baseline when self reported alcohol consumption is at harmful or hazardous levels blood will also be taken at follow-up. If there are no abnormalities at baseline with self reported alcohol consumption at harmful or hazardous levels no blood will be taken at follow-up as repeat testing not clinically indicated and not informative as a measure of alcohol consumption.

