### Secondary outcome measures

Secondary outcome measures are: the number (proportion) of days abstinent during the past 90 days; two time to event measures: (i) time to first drink; (ii) time to first heavy drinking day “relapse”, defined as three consecutive days drinking ≥ 6 standard drinks for a man and ≥ 4 standard drinks in a day for women) assessed using the TLFB [75,76]; the Depression, Anxiety and Stress Scale scores [87], and Days out of role from the Brief Disability Questionnaire [88].

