### Follow-up

At the end of treatment and at three and six months after treatment completion, participants will be reassessed by an experienced independent research assistant blind to treatment condition. Participants will be reassessed on the main outcome measures in addition to the Drinker Inventory of Consequences (DRINC) [89], Kushner’s Alcohol Outcome Expectancies Questionnaire [74], the OTI, the Penn Craving Scale [77], Alcohol Expectancies Social Anxiety (AESES) [91], University of Rhode Island Change Assessment (URICA) [79], and the Health Service Utilisation questions [80].

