### Analyses

Random effects regression models will be used to compare the efficacy of the treatment conditions on outcome measures from an intention to treat perspective. Random effect regression models (also known as hierarchical linear or mixed models) have been used in clinical trials involving relapse, and are suited to repeated measures, missing observations, and longitudinal data [99]. Random effects regressions can also account for variance associated with the clustering found with group treatment and multiple treatment sites. Cox regression will be used to determine time from baseline to first drink, time to first heavy drink. Last-point carried forward or multiple imputation will be used to determine the scores of participants who drop-out and are not located at follow-up.

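### The only stated TLFB recall is 28 days, but three secondary drinking outcomes scored from the TLFB need 90 days or an unbroken daily record; the sections must be reconciled

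*Protocol article*

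**What the plan says.** All references are to the protocol article.

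- **Assessment.** The list of study measures includes "the Timeline Follow-Back (TLFB) method for quantifying alcohol consumption over the previous 28 days". Table 1 gives the TLFB at pre-treatment, post washout, post treatment, 3 months and 6 months. It attaches no other recall period to any of these visits.
- **Secondary outcome measures.** Three outcomes are attributed to the TLFB. One is "the number (proportion) of days abstinent during the past 90 days". The others are "two time to event measures: (i) time to first drink", and time to first heavy drinking or relapse, the latter "defined as three consecutive days drinking ≥ 6 standard drinks for a man" (with a lower threshold for women).
- **Analyses.** "Cox regression will be used to determine time from baseline to first drink, time to first heavy drink".
- **Follow-up.** "At the end of treatment and at three and six months after treatment completion, participants will be reassessed". No recall period is given here.
- **Treatment and treatment sites.** Participants keep daily diaries that record drinks. The diaries are described as part of therapy and are not named as the source of any outcome. None is described after treatment ends.

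**The concern.** A 28-day record cannot supply a 90-day count. Nor can it date the first drink, or the first run of three heavy drinking days, across visits that lie about 13 weeks apart. The same instrument is therefore given one window where it is described and a longer one where it is scored.

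If interviewers follow the stated 28 days, three things happen:

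- Days abstinent has to be extrapolated from under a third of its window.
- A person who lapses in a gap and is still drinking when the next window opens has the event dated late.
- A person who lapses and stops within a gap is recorded as never having drunk.

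These outcomes bear directly on the part of Hypothesis 2 about keeping consumption low for longer. The problem lies in data collection, so an analysis plan written later cannot repair it: days not asked about at the visit are lost.

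**Working it through.** The document states no coverage figure, so there is none to reproduce. The check is arithmetic on the stated schedule.

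**Inputs**

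- Recall per TLFB: 28 days (Assessment).
- Abstinence window: 90 days (Secondary outcome measures).
- Follow-up visits at 3 and 6 months after treatment: two intervals of about 91 days, 182.5 days in all (Follow-up).
- Baseline assessment to end of treatment: about 91 days at the planned pace (28 days of washout + 9 weekly sessions × 7 = 63 days). The maximum is 5 months from initial assessment, about 152 days (Procedure).
- Time origin: baseline (Analyses).

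**Formula.** Share unobserved = 1 − (days covered by TLFB windows) / (days in the period).

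**Abstinence outcome.** 28/90 = 31.1% observed. 90 − 28 = 62 days, or 68.9%, unobserved.

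**Each post-treatment interval.** 91 − 28 = 63 days blank; 63/91 = 69.2%. Over the whole six months: 1 − 56/182.5 = 69.3%.

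**Baseline to 6 months.** Four windows fall after baseline: post washout, post treatment, 3 months and 6 months, so 4 × 28 = 112 days. The pre-treatment TLFB looks back before baseline and adds no days to this period.

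- Planned pace: 91 + 182.5 = 273.5 days; 1 − 112/273.5 = 59.0% unobserved.
- Slowest permitted pace: 152 + 182.5 = 334.5 days; 1 − 112/334.5 = 66.5% unobserved.

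**If complete treatment-period diaries were used as well.** All days up to the end of treatment would then be covered.

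- Planned pace: 1 − (91 + 56)/273.5 = 46.3% unobserved.
- Slowest pace: 1 − (152 + 56)/334.5 = 37.8% unobserved.
- After treatment the gap stays at 69.3%.

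**Illustration, under an assumed constant daily hazard.** Let p be the probability of a first drink within a 91-day interval. The share of those first drinks that start in the 63 unrecorded days is [1 − (1 − p)^(63/91)] / p. This gives 72% for p = 0.25, 76% for p = 0.50 and 82% for p = 0.75. The values of p are assumptions; the document gives none.

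**The case against.** The strongest reply is that the article gives two windows and does not rank them. The 28-day phrase appears once, in a list of measures, while the outcome definition itself implies a 90-day TLFB. A longer recall at follow-up may well have been intended, and visit-specific interview windows could sit in a fuller protocol. This stands in part. It means the coverage figures hold only if the 28-day window is followed. It does not remove the conflict: the measures list points to Table 1, which repeats the TLFB at every visit, and no longer recall is stated anywhere.

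The diaries are a second reply. They could narrow the gap during treatment if they were complete and used, but the outcomes are attributed to the TLFB and no diary is described after treatment.

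A third reply is that the event times could be analysed as interval-censored. That deals with late dating. It cannot reveal a lapse that began and ended inside a gap.

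Some stronger readings are tempting but not supported:

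- **A reader might start the clock at randomisation and call the first weeks of follow-up blank.** The Analyses section says baseline, and Table 1 places a TLFB at post washout that covers about the first month. From baseline the unobserved share is 59% to 67%, so two thirds is the upper end and not a general figure.
- **A reader might infer that nothing else measures how long gains last.** Drinks per drinking day and the SADQc are repeated at post treatment, 3 months and 6 months, and the planned random effects models suit repeated measures.
- **A reader might infer that the Cox hazard ratio is biased.** Nothing in the document shows this. Simulations need assumed drinking rates and episode lengths, and under constant hazards they leave the hazard ratio roughly unchanged. What is at risk is events and their dates.

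**Conclusion.** The sections contradict each other on the TLFB window, and as written the three secondary outcomes do not match the data to be collected. If the 28-day recall is followed, 31% of the abstinence window is observed, 69% of each post-treatment interval is blank, and 59% to 67% of the time from baseline to 6 months is unobserved.

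These figures assume 91-day follow-up intervals, a treatment phase of 3 to 5 months from assessment, and a TLFB at post washout as in Table 1. The direction of the conclusion does not depend on these choices: any 28-day record falls short of 90 days and of a three-month interval.

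This should be fixed before follow-up data are collected. It affects secondary outcomes only. The primary drinking measure from the TLFB can be computed from 28 days and stands.

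**What to change.** Reconcile the Assessment, Secondary outcome measures and Analyses sections in one of two ways.

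1. **Extend the recall (preferred).** State in the Assessment section and Table 1 that the TLFB at post washout, post treatment, 3 months and 6 months covers every day since the last covered day, and at least 90 days at the 3- and 6-month visits. Keep the last 28 days of each record for drinks per drinking day. Treat first drink and first heavy drinking in any stretch still uncovered as interval-censored.
2. **Keep 28 days.** Redefine abstinence as the proportion of the past 28 days. Then either drop the two event-time outcomes, or analyse them as interval-censored and state that lapses confined to a gap go undetected.

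A 90-day TLFB at pre-treatment would put baseline abstinence on the same scale as follow-up. It is optional, since the arms can be compared at follow-up without it.

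The cost of the first option is a longer calendar interview and longer recall for the earlier days, at visits already scheduled; no extra visits or participants are needed. The second option costs only wording, but it gives up information on when drinking resumes.

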### Hypotheses

1. Participants who receive treatment for alcohol use problems alone will show reductions in alcohol consumption and symptoms of social phobia and improvements on secondary outcomes.

2. Participants who receive the integrated treatment for alcohol use problems and social phobia will show significantly greater improvements in terms of alcohol consumption, social phobia and quality of life compared with those in the alcohol treatment alone. They will maintain a lower rate of alcohol consumption for longer than the alcohol treatment alone group and will have greater improvements on measures of general health and functioning.

3. Participants in the integrated treatment condition will have a lower rate of treatment attrition than participants in the alcohol treatment alone intervention.

4. Higher levels of alcohol dependence will result in relatively poorer outcomes for the integrated treatment.

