### Primary outcome measures

The primary outcomes for social anxiety disorder will be reductions in measures of social anxiety disorder: the Social Phobia Scale and Social Interaction Anxiety scale [83]. The primary outcome measures for alcohol are a reduction in the number of standard drinks per drinking day, assessed using the TLFB [75,76] and in the Severity of Alcohol dependence Questionnaire (SADQc) [84]. Quality of Life will be assessed by the SF12 [85].

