### Procedure

After baseline assessment, all participants will complete a pre-treatment session of motivational interviewing followed by a 1 month “washout” period of abstinence. Symptoms of social anxiety (SPS and SIAS), general anxiety and depression (DASS) will then be reassessed. After reading and signing a written information and consent form, participants will be individually randomised by the sealed envelope method to one of two treatment conditions, of either: i) Treatment for alcohol use disorder comprising 9 weekly sessions of individual CBT for alcohol use disorder; OR ii) Treatment for alcohol use disorder and social anxiety disorder comprising 9 weekly sessions of integrated individual CBT for alcohol use disorder and anxiety disorder.

Each therapy session will last 60 to 90 minutes and will be conducted by one therapist (Clinical Psychologist). Both treatment conditions will have the same therapists and equal exposure to face-to-face treatment, approximately 10–15 hours, over a total of approximately three to five months.

Participants will be encouraged to attend treatment sessions weekly where possible, but will be given a maximum time frame of 5 months from initial assessment in which to complete treatment. Post and follow up assessment time points will be calculated from the end of all treatment sessions (1 motivational interviewing session plus 9 treatment sessions).

Participants will be considered non-completers if they miss more than 2 treatment sessions, or if they fail to complete the course of treatment within five months from assessment. Therapists will make at least 3 attempts to reschedule missed appointments, followed by a handwritten note two weeks after the last phone contact to i) acknowledge client’s decision to leave treatment, ii) encourage return to treatment, and iii) provide information about how this can be achieved. Participants who nevertheless choose to discontinue treatment will be contacted for post and follow up assessments calculated as if treatment were completed 3 months from the initial assessment.

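### By Table 1 the SF12 is the only primary self-report or interview measure not repeated after washout, so its sole pre-randomisation value predates the washout month; the cost is possible loss of precision, not bias

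*Protocol article*

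**What the plan says.** Under Primary outcome measures, the protocol article states "Quality of Life will be assessed by the SF12 [85". Hypothesis 2 claims that the integrated arm will show "significantly greater improvements in terms of alcohol consumption, social phobia and quality of life compared with those in the alcohol treatment alone".

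Table 1 (Assessment section) fixes the visits. The rows "Social Phobia Scale and Social Interaction Anxiety Scale (SPS/SIAS) [83", "Time Line Follow Back (TLFB) [76" and "Severity of Alcohol Dependence Questionnaire (SADQc) [84" carry a plus sign at post washout, as does the secondary DASS-21. The row "General Health functioning SF12 [85" carries a minus sign there and a plus sign at pre treatment, post treatment, 3 months and 6 months.

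The Procedure section gives the order of events: baseline assessment, a motivational interviewing session, a month of abstinence, a reassessment, then randomisation. It describes the reassessment as follows: "Symptoms of social anxiety (SPS and SIAS), general anxiety and depression (DASS) will then be reassessed". The sections on treatment and on the pre-treatment session give the length of the washout as at least one month.

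**The concern.** A baseline covariate helps most when it is measured close to randomisation, in the state from which participants start treatment. Here the SF12 is taken before a motivational session and a month or more of directed abstinence. That month may change self-rated health, and by different amounts in different people. The protocol accepts the general idea: the Assessment section asks for three days of low-risk drinking before assessment to limit the transient effects of alcohol on functioning, and social anxiety, general anxiety and depression are measured again after the washout.

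Two things are at stake. First, if the washout reorders participants on the SF12, the older value explains less of the follow-up variance, and the quality-of-life comparison is less precise than the same sample could give. Second, improvement on the SF12 counted from pre-treatment mixes washout change with treatment change. For SPS/SIAS the two can be told apart. For the SF12 they cannot, and no later analysis can recover a visit at which it was not measured.

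**Working it through.** The plan states no figure for this point, so there is none to reproduce. The check has two parts.

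**1. Schedule.** The rows listed as primary in Table 1:

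| Measure | Pre treatment | Post washout | Named in the Procedure sentence on reassessment |
|---|---|---|---|
| SPS/SIAS | + | + | yes |
| TLFB | + | + | no |
| SADQc | + | + | no |
| SF12 | + | - | no |
| Blood tests | + | - | no |

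Of the four self-report or interview rows, three are repeated and the SF12 is not. The blood tests ("Blood for LFTs, FBC, CDT, Electrolytes") are not repeated either, but they are laboratory tests with only a conditional repeat at 3 months. Text and table differ on TLFB and SADQc; they agree that the SF12 is not repeated. With a washout of at least one month between baseline and randomisation, the SF12 baseline is at least about one month old at randomisation. Figure 1 is not shown, so the place of randomisation rests on the order of the Procedure text.

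**2. Possible size.** The documents give no correlation between SF12 visits, so the following are assumptions: r1, the correlation of the pre-washout SF12 with follow-up, lies between 0.3 and 0.5; r2, that of a post-washout SF12, lies between 0.5 and 0.7. For one follow-up visit adjusted for one baseline, residual variance is proportional to 1 - r². The ratio, new to old, is (1 - r2²)/(1 - r1²).

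| r1 | r2 | Ratio | Reduction |
|---|---|---|---|
| 0.5 | 0.5 | 0.75/0.75 = 1.00 | 0% |
| 0.5 | 0.6 | 0.64/0.75 = 0.85 | 15% |
| 0.3 | 0.5 | 0.75/0.91 = 0.82 | 18% |
| 0.4 | 0.6 | 0.64/0.84 = 0.76 | 24% |
| 0.5 | 0.7 | 0.51/0.75 = 0.68 | 32% |
| 0.3 | 0.7 | 0.51/0.91 = 0.56 | 44% |

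The assumed ranges therefore allow a reduction from 0% to about 44%.

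In terms of power, take the 168 participants of the sample size section, 168/2 = 84 per arm, two-sided alpha 0.05, and the normal approximation: power = Φ(d / √((1 - r²) × 2/84) - 1.96).

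- d = 0.5 (the planned effect): r = 0.5 gives Φ(3.742 - 1.96) = 0.963; r = 0.6 gives Φ(4.051 - 1.96) = 0.982.
- d = 0.3 (illustration only): r = 0.5 gives 0.612; r = 0.6 gives 0.681.
- The difference detectable with 80% power, 2.8016 × √(1 - r²) × √(2/84), goes from 0.374 at r = 0.5 to 0.346 at r = 0.6.

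The formula is for a single follow-up. The plan intends a repeated-measures random effects model, so these figures indicate scale only.

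**The case against.** The strongest reply is that nothing here is an error. Table 1 and the Procedure text agree that the SF12 is not repeated, and the choice follows a pattern: the Sheehan Disability Scale, days out of role and the DRINC are also not repeated after washout. The Procedure text describes that assessment as one of symptoms, while Table 1 labels the SF12 a measure of functioning. This stands. The omission may well be deliberate, and the point is an improvement, not a correction.

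A reader might infer that the old baseline biases the quality-of-life comparison. The documents do not support that. The SF12 is taken before randomisation in everyone, and the motivational session and washout are common to both arms, so any drift is unrelated to allocation.

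No section makes post washout the analysis baseline for any outcome. The Procedure section calls the pre-washout assessment the baseline, and the Analyses section does not name a covariate. It also counts the motivational session among the treatment sessions, so change from pre-treatment is a legitimate measure of the whole programme. Hypothesis 1 names alcohol consumption, social phobia and secondary outcomes, not quality of life. Separating washout change from treatment change on the SF12 therefore helps interpretation but serves no stated hypothesis.

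Finally, the gain is assumed. Nothing in the documents shows that a post-washout SF12 would predict follow-up better. If the washout leaves participants' ranking on the SF12 unchanged, the gain is near zero. At the planned effect size, unadjusted power with 84 per arm is already about 0.90. All of this limits the weight of the point. None of it shows a real drawback to measuring the SF12 once more.

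**Conclusion.** The point holds as an optional refinement. On Table 1, the SF12 is the only primary self-report or interview measure without a post-washout value, and its single pre-randomisation value predates the motivational session and at least one month of washout. The word only depends on the table, since the Procedure sentence omits TLFB and SADQc as well.

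The comparison of arms is valid either way. The possible loss is precision on one outcome of hypothesis 2, of unknown size: 0% to about 44% of residual variance under the assumed correlations, with little effect on power at d = 0.5 and a more visible one at smaller effects. A reader might take a mid-range figure, such as 15% to 32%, as the expected gain. That would be unsafe, because those values come from choosing pairs in which the correlation rises by 0.1 to 0.2, and no document supports any particular rise. The loss of interpretability is certain but modest: SF12 change over the washout will be unknown.

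**What to change.** - In Table 1, change the SF12 entry under post washout from minus to plus.
- In the Procedure section, add the SF12 to the sentence listing what is reassessed after washout, and reconcile that sentence with Table 1 on whether TLFB and SADQc are collected then.
- Use the post-washout, pre-randomisation SF12 as a baseline covariate in the SF12 comparison. Keep the pre-treatment value to describe change during washout; it may also enter the model as a second covariate.

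The cost is a few minutes of participant time at an assessment that already takes place. No extra visit or staff is needed, and no figure in the sample size section changes.
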